## Abstract

**Background:**

Early detection of oesophageal cancer improves outcomes; however, the optimal strategy for identifying patients at increased risk from the pre-cancerous lesion Barrett’s oesophagus (BE) is not clear. The Cytosponge, a novel non-endoscopic sponge device, combined with the biomarker Trefoil Factor 3 (TFF3) has been tested in four clinical studies. It was found to be safe, accurate and acceptable to patients.

The aim of the BEST3 trial is to evaluate if the offer of a Cytosponge-TFF3 test in primary care for patients on long term acid suppressants leads to an increase in the number of patients diagnosed with BE.

**Methods:**

The BEST3 trial is a pragmatic multi-site cluster-randomised controlled trial set in primary care in England. Approximately 120 practices will be randomised 1:1 to either the intervention arm, invitation to a Cytosponge-TFF3 test, or the control arm usual care. Inclusion criteria are men and women aged 50 or over with records of at least 6 months of prescriptions for acid-suppressants in the last year. Patients in the intervention arm will receive an invitation to have a Cytosponge-TFF3 test in their general practice. Patients with a positive TFF3 test will receive an invitation for an upper gastro-intestinal endoscopy at their local hospital-based endoscopy clinic to test for BE.

The primary objective is to compare histologically confirmed BE diagnosis between the intervention and control arms to determine whether the offer of the Cytosponge-TFF3 test in primary care results in an increase in BE diagnosis within 12 months of study entry.

**Discussion:**

The BEST3 trial is a well-powered pragmatic trial testing the use of the Cytosponge-TFF3 test in the same population that we envisage it being used in clinical practice. The data generated from this trial will enable NICE and other clinical bodies to decide whether this test is suitable for routine clinical use.

**Trial registration:**

This trial was prospectively registered with the ISRCTN Registry on 19/01/2017, trial number ISRCTN68382401.

**Electronic supplementary material:**

The online version of this article (10.1186/s12885-018-4664-3) contains supplementary material, which is available to authorized users.

## Background

Incidence of oesophageal adenocarcinoma (EAC) has increased six-fold since the 1970s and carries a dismal prognosis (13% 5-year survival) despite advances in neo-adjuvant therapy and surgery [1]. Clinical guidelines have focused on urgent referral for those with alarm symptoms, specifically dysphagia, chronic gastro-intestinal bleeding, weight loss, persistent vomiting, anaemia or an epigastric mass [2]. Routine referral is advised for those with reflux symptoms that persist despite recommended lifestyle and pharmacological management strategies [3]. General Practice (GP) referral rates vary widely and low endoscopy referral rates have been linked with poor outcomes from oesophageal cancer [4].

Approximately 3 to 6% of individuals with reflux predominant symptoms may have Barrett’s oEsophagus (BE), the precursor lesion to EAC. However, only 20 to 25% of patients with BE are diagnosed [5]. It is estimated that the burden of EAC could be reduced by up to 50% as a result of increasing the proportion of individuals with reflux predominant symptoms who are investigated [6]. This is a formidable task since dyspepsia and gastro-oesophageal reflux disease (GERD) affect between 5 and 20% of the population [7] and account for up to 10% of GP consultations in the UK.

Endoscopic treatment of BE, which progresses through dysplastic and superficially invasive stages, can prevent the development of EAC [8]. Indeed, endoscopic treatment is now recommended for patients with low and high grade dysplasia following new randomised controlled trial evidence [9, 10]. By identifying and referring to endoscopy those most likely to have BE, it should be possible to reduce mortality from EAC in patients with reflux who would not otherwise receive endoscopy.

### Cytosponge diagnostic test for Barrett’s oESophagus

A non-endoscopic diagnostic modality for BE has been developed which involves a device called the Cytosponge™ combined with molecular biomarker Trefoil Factor 3 (TFF3) [11] (Fig. 1).

**Fig. 1 Fig1:**
[figure not shown]
(**a**) Cytosponge™ expanded (left) and in gelatin capsule (right) (**b**) representative picture of positive TFF3 staining in a sample from a patient with BE (× 20 magnification)

The Cytosponge™ consists of a Class I, non-CE marked 3 cm diameter, polyester, medical grade mesh sphere on a string, compressed within a gelatine capsule. The capsule is swallowed while holding onto the string. After 5 min, the gelatine capsule has dissolved allowing the sphere to expand. Using the string the sphere is pulled from the stomach to the oesophagus and mouth thus collecting cells from the whole of the BE segment [12], as well as from the squamous oesophagus and oropharynx. The sample is put into a preservative, processed, and assessed for the presence of BE via immunohistochemical staining for TFF3.

A series of four clinical studies have been carried out so far with the following findings (see Table 1). First, no serious adverse events were attributed to the Cytosponge™ after administering this test over 2000 patients, showing that it is a safe intervention [11, 13–16]. Second, the Cytosponge™ is acceptable to patients with a mean score of 6.0 (95%CI 5.0–8.0) on a visual analogue scale from zero (worst experience) to 10 (best experience) reported by patients [11, 13–16]. Third, the Cytosponge intervention was shown to be transferable to the NHS: 27 nurses were trained with a single training session in 11 sites and sample processing was run in an NHS pathology laboratory [13, 17]. Fourth, a feasibility study conducted in 504 patients in 11 general practices showed that the intervention can be applied to primary care [13]. Fifth, the Cytosponge™-TFF3 test was found to be accurate for diagnosing BE regardless of patient cohort or study setting. Last, this test is cost-effective in comparison to the usual care. A micro-simulation model suggested a gain of 0.015 QALYs (Quality adjusted life years) and an incremental cost effectiveness ratio (ICER) of $15,700 per QALY for Cytosponge™ versus endoscopic diagnosis of BE followed by endoscopic treatment [18].

**Table 1 Tab1:** Studies summary, sensitivity and specificity of the Cytosponge™-TFF3 test per segment length

Study Ref n#	Publication Year	Study type	Setting	BE length	Sensitivity % (95% CI)	Specificity % (95% CI)
Pilot [14]	2008	Cohort	2^ary^ care	≥C1	78.0 (64.0–89.0)	94.0 (87.0–98.0)
BEST1 [12]	2010	Prospective	1^ary^ care	≥C1	73.3 (44.9–92.2)	93.8 (91.3–95.8)
				≥C2	90.0 (55.5–99.7)	93.5 (90.9–95.5)
BEST2 [13]	2014	Case:control	2^ary^ care	≥C1	79.5 (75.9–82.9)	92.4 (89.5–94.7)
				≥C2	83.9 (80.0–87.3)	
				≥C3	87.2 (83.0–90.6)	
CASE1 [15]	2015	Cohort	2^ary^ care	≥C1 or ≥ M3 ≥C3	95.4 (86.9–98.9) 96.8 (83.7–99.5)	N/A

### Rationale

Our long-term vision is for the Cytosponge™-TFF3 technology to be adopted as a triage test within the standard primary care clinical pathway for patients on treatment with acid suppressants (proton pump inhibitors (PPIs) or H2 receptor antagonists (H2RAs)) who do not fulfil the referral criteria for endoscopy. This strategy will increase the proportion of patients diagnosed with BE, and in turn allow for endoscopic therapy and monitoring for those at greatest risk of EAC.

### Objectives

Primary and secondary objectives, and endpoints are summarised in Table 2 and described below.

**Table 2 Tab2:** BEST3 Trial objectives and endpoints

Objective	Endpoint	Usual care arm	Intervention arm
Primary objectives			
1. To compare histologically confirmed BE diagnosis between intervention and control	BE diagnosis within 12 months of joining the study (excluding BE found on random 12 month research endoscopy that will occur following 12 month snapshot).	Anonymised data aggregated by sex and age group from: - GP databases - Confirmed by upper GI endoscopy (biopsy result) as recorded in the GP record within 12 months	Anonymised data aggregated by sex and age group from: - GP databases - Confirmed by upper GI endoscopy (biopsy result) as recorded in the GP record within 12 months In addition, for patients with Cytosponge™ -TFF3 test: - Endoscopy record and pathology results
Secondary objectives			
(i) To evaluate the cost of the Cytosponge™-TFF3 test versus usual care Objective (ii) To evaluate the cost-effectiveness of the Cytosponge™-TFF3 test versus usual care	(i) Mean cost per patient receiving the Cytosponge™-TFF3 test versus usual care. Costs to include costs of diagnosis using the Cytosponge™-TFF3 test, endoscopies and biopsies, endotherapy, oesophagectomy, medications, and follow-up in primary and secondary care. (ii) Incremental cost per QALY gained of the Cytosponge™-TFF3 test versus usual care	(i) Volume of resource use (endoscopies and biopsies, endotherapy, oesophagectomy, medications, and follow-up in primary and secondary care) from patient records. Unit costs (of each item of resource use) from published sources. (ii) Calculation of incremental cost per QALY gained to be based on a pre-existing model, supplemented with new data from the Trial.	(i) Volume of resource use (Cytosponges™, endoscopies and biopsies, endotherapy, oesophagectomy, medications, and follow-up in primary and secondary care) from patient records. Unit costs (of each item of resource use) from published sources. (ii) Calculation of incremental cost per QALY gained to be based on a pre-existing model, supplemented with new data from the trial.
To assess the diagnostic accuracy of the Cytosponge™ in primary care	Positive Predictive Value (PPV), Negative Predictive Value (NPV) in relation to the length of BE	N/A	- PPV: proportion of TFF3 positive results confirmed to have BE by endoscopy - NPV: proportion of TFF3 negative cases confirmed to not have BE by endoscopy (10% endoscopy)
To assess diagnostic performance of Cytosponge™ in detecting severity for BE	Score of BE severity based on BE biopsy results	N/A	Endoscopy reports for participants
To report on the sampling adequacy	Inadequacy rate (same as BEST1 and BEST2)	N/A	CRF to capture: - Sample sufficient to generate result - Proportion of Cytosponge™ samples with < 5 and < 1 columnar cells (minimal standard)
To confirm the endoscopy referral rate in the intervention arm	Proportion positive out of all adequate TFF3 tests and out of all patients swallowing a Cytosponge™ at least once	N/A	Cytosponge™-TFF3 test results
To report on patient acceptability for Cytosponge™	(i) Willingness: proportion of patients offered Cytosponge™ test who accept (ii) Cytosponge™ swallowing failures (iii) Increased and decreased cancer worry due to procedure and results (iv) Long term emotional or physical harm caused by procedure (v) Test experience (vi) Willingness to have repeat procedure	N/A	(i) Number of patients invited vs those consenting to Cytosponge™-TFF3 test (ii) Number of patients who fail to swallow and number of attempts Acceptability measures at baseline: (iii) STAI-6 (iv) Perceived risk of oesophageal cancer Acceptability measures at day 7–14: (iii) Perceived risk of oesophageal cancer (iv) STAI-6 (v) A visual analogue scale to rate experience (v-vi) the Inventory to Assess Patient Satisfaction, (iii – v) up to 30 qualitative patient interviews
To assess physician/nurse acceptability of the Cytosponge™	Experience and acceptability of Cytosponge™: administration, skills, reliability, side effects, user information	N/A	Qualitative interviews of clinical staff
To report on the safety of the Cytosponge™ in primary care	Any ADE/ARs reported by patients up to 7 days post swallowing	N/A	Contact card given in case of ADE/SADE and 7-day telephone call
(i) To understand how much BE is missed in current management of patients (ii) To compare undiagnosed BE in general population vs those who have been tested with Cytosponge™-TFF3	- BE at 12 months - PPV for endoscopy referral, i.e. Cytosponge™ vs current GP criteria for referring for an endoscopy to look for BE	12 month endoscopy for 10% of patients not requiring a clinically indicated endoscopy in time period of the study	Confirmatory endoscopy for patients with positive result and endoscopy findings from patients with negative result who accept research endoscopy at 12 months.
To assess prevalence of benign oesophageal conditions	Prevalence of oesophageal conditions aside from BE in primary care population consulting with reflux symptoms	Endoscopy findings in 10% patients endoscoped	Endoscopy findings in 10% patients endoscoped and on Cytosponge™ test (via pathology assessment)
Epidemiology: (i + ii) To confirm the prevalence (and incidence) of BE in both arms (iii) To confirm the prevalence (and incidence) of OC diagnosis (by stage) in both arms (iv) To confirm the prevalence (and incidence) diagnosis cancers of the gastric cardia (by stage) in both arms (v) To produce a model to predict the reduction in EAC related mortality from this strategy	(i) Diagnosis of BE (ii) Diagnosis BE with dysplasia (iii) Diagnosis of oesophageal cancer (OC) + stage at diagnosis (iv) Diagnosis of cancer of the gastric cardia + stage at diagnosis (v) Percentage of expected reduction in EAC mortality based on prevalence of BE if Cytosponge™ test introduced	(i-iv) Aggregate data from GP databases	(i-iv) Aggregate data from GP databases (i-iv) Endoscopy data from 10% endoscopy offered at 12 months (i-iv) Cytosponge™ patients: - Cytosponge™ findings - Endoscopy findings
10% endoscopy invitation across both arms: (i) Acceptability of endoscopy (ii) Perceptions around Cytosponge™ use and reliability (iii) Number of BE diagnoses 12 months after negative TFF3 tests	(i) Comparisons between acceptance of invitation to endoscopy compared to Cytosponge™ test (ii) Proportion of patients with Cytosponge™ test who take up invitation to endoscopy (iii) Number of BE diagnosis in TFF3 negative patients in intervention arm	(i) 10% endoscopy: uptake of invitation to endoscopy	(i) 10% endoscopy: uptake of invitation to endoscopy for all participants who have not received the CytospongeP™ P (excluding ineligible patient and non-attendees for Cytosponge™) (i) CytospongeP™ Ptest invitation uptake (ii) Endoscopy uptake amongst patients with previous Cytosponge™ test (iii) BE diagnosis amongst patients with previous Cytosponge™ test
Objective			
Longer-term objectives			
Epidemiology: For up to 10 years, to confirm the prevalence (and incidence): (i + ii) of BE in both arms (iii) of OC diagnosis (by stage) in both arms (iv) of cancers of the gastric cardia (by stage) in both arms (iv) To undertake modelling to predict the reduction in EAC related mortality from this strategy	(i) Diagnosis of BE (ii) Diagnosis of BE with dysplasia (iii) Diagnosis of OC + stage at diagnosis (iv) Diagnosis of cancer of the gastric cardia + stage at diagnosis (v) Percentage of expected reduction in EAC mortality based on prevalence of BE if Cytosponge™ test introduced	(i-iv) Anonymised data from cancer registry flagging- conducted anonymously via novel encryption method (v) Based on BE prevalence, prevalence of BE with dysplasia, flagging with the cancer registry, ONS and HES datasets	(i-iv) Anonymised data from cancer registry flagging- conducted anonymously via novel encryption method (v) Based on BE prevalence, prevalence of BE with dysplasia, flagging with the cancer registry, ONS and HES datasets
Research and Development (including in future studies)	Genetic and biochemical risk factors for disease progression (germline and somatic variants and other biomarkers) including targeted, exome level and whole genome sequencing.	10% patients who have endoscopy- surplus material from biopsies	- Surplus Cytosponge™ material - Saliva samples (for TFF3 positive patients only) - Surplus endoscopy biopsies

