#### Invitation for research endoscopies - 10% of patients who do not require diagnostic endoscopy (all arms)

10% of the total number of study participants who have not had an endoscopy during the study will be invited for a research endoscopy at 12 months after entry into the study, including participants who have declined the original Cytosponge™-TFF3 intervention. Since BEST3 will be assessing the acceptability of endoscopy compared with Cytosponge™-TFF3, the intervention here will be “invitation to endoscopy”. Participants to be invited will be selected at random using the random selection function in practice databases. They will receive an invitation letter for a research endoscopy at their local hospital-based endoscopy clinic including an endoscopy-specific BEST3 Patient Information Sheet and a consent form.

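### Table 2's Epidemiology row counts the 12-month research endoscopies for the intervention arm only, so the two arms' BE, dysplasia and cancer figures are ascertained by different rules

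*Protocol article*

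**What the plan says.** **Who is endoscoped.** The Design section and the section on invitation for research endoscopies both provide for a random 10% of patients without a study-period endoscopy to be invited at about 12 months, in each arm. In the intervention arm this means "including participants who have declined the original Cytosponge™-TFF3 intervention". The sampling is therefore symmetric.

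**Epidemiology row of Table 2.** The first aim is "To confirm the prevalence (and incidence) of BE in both arms". Parallel aims follow for oesophageal and gastric cardia cancer, and BE with dysplasia is among the endpoints. For usual care the only source listed is "i-iv) Aggregate data from GP databases". For the intervention arm the same source appears, followed by "i-iv) Endoscopy data from 10% endoscopy offered at 12 months" and by the Cytosponge and endoscopy findings of tested patients.

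**Missed-BE row of Table 2.** Objective (ii) is "To compare undiagnosed BE in general population vs those who have been tested with Cytosponge™-TFF3". Usual care contributes "12 month endoscopy for 10% of patients not requiring a clinically indicated endoscopy in time period of the study". The intervention arm contributes "Confirmatory endoscopy for patients with positive result and endoscopy findings from patients with negative result who accept research endoscopy at 12 months".

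**Elsewhere.** The primary endpoint excludes BE found at the research endoscopies and says that they follow the 12-month snapshot. The benign-conditions row uses the 10% endoscopies in both arms. The longer-term epidemiology row lists the same registry sources for both arms.

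**The concern.** Un-endoscoped patients in either arm carry undiagnosed BE, and looking for it finds cases whatever the arm. If those cases are credited to one arm only, that arm shows more BE, more dysplasia and possibly more cancer, for a reason unrelated to the offer of the test. This would happen even if the offer had no effect.

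The Cytosponge and confirmatory-endoscopy findings listed for the intervention arm are not the problem, because they are the intervention at work. The research endoscopies are a measurement applied to both arms and should be handled alike in both.

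The missed-BE row raises a smaller question. It sets patients who chose to be tested against a random sample of usual care. That is a legitimate description, but randomisation does not protect it, and the row does not say so.

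**Working it through.** **1. Can the usual-care findings arrive by another route?** Endoscopy results are copied to the GP (Endoscopy procedures), so they may eventually reach the GP record. But Table 2 places the research endoscopy after the 12-month snapshot. The 12-month GP extract therefore does not contain them. No other section adds them to the usual-care cell of this row.

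**2. Reproduce the plan's rates.** Inputs from Sample size calculations and Table 7: BE prevalence 4% (lower end of 4–5%), usual-care diagnosis 10% × 6% = 0.6%, sensitivity 85%, uptake 27%.

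Intervention diagnosis rate
= 0.27 × 0.85 × 0.04 + 0.73 × 0.006 + 0.27 × 0.15 × 0.006
= 0.00918 + 0.00438 + 0.00024 = 1.380%, the plan's 1.4%.

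Comparing 0.600% with 1.380% at 90% power and two-sided 5%, without continuity correction, gives 3382 per arm, or 6764 in total. This is the plan's amended figure exactly, so these are the plan's own rates.

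**3. Expected diagnoses.** Total 15,656, taken as equal arms: 7828 each.
- Usual care: 7828 × 0.006 = 47
- Intervention: 7828 × 0.01380 = 108
- Difference: 61

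**4. BE available to the research endoscopies.** Inviting 10% of un-endoscoped patients reaches 10% of the undiagnosed BE. Multiply by endoscopy uptake *u*, which the document does not give; 15–50% is assumed.
- Usual care: undiagnosed 4.00% − 0.60% = 3.40%. Cases found = 7828 × 0.0340 × 0.10 × *u* = 26.6*u*, or 4.0–13.3.
- Intervention: undiagnosed 4.00% − 1.38% = 2.62%. Cases found = 7828 × 0.0262 × 0.10 × *u* = 20.5*u*, or 3.1–10.3.

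**5. Effect of counting one arm only.** Relative to the expected difference of 61: 3.1/61 = 5% and 10.3/61 = 17%. At 5% prevalence the intervention rate becomes 1.610%, the difference 7828 × 0.01010 = 79, and the added cases 7828 × 0.0339 × 0.10 × *u* = 4.0–13.3, again 5–17%.

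**6. If the offer had no effect.** Both arms then have 0.6% diagnosed clinically. At 4% prevalence, one-sided counting adds 0.034 × 0.10 × *u*. With *u* = 20% the intervention rate becomes 0.668% (ratio 1.11); with *u* = 50%, 0.770% (ratio 1.28). At 5% prevalence the ratios are 1.15 and 1.37. Counting alike gives 1.0.

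**7. Missed-BE row.** With Table 1's BEST2 specificity of 92.4%, BE in TFF3-negatives is 0.15 × 0.04 / (0.15 × 0.04 + 0.924 × 0.96) = 0.67%. In un-endoscoped usual care it is 0.034/0.90 = 3.8%. Among all un-endoscoped intervention patients, tested or not, it is about 3.0%: 0.0262 over an un-endoscoped fraction of 0.73 × 0.9 + 0.27 × 0.893 × 0.9 = 0.874.

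**The case against.** **A list of sources is not an analysis rule.** The row's verb is to confirm, no between-arm test is stated for it, and nothing says that research cases are added to the GP count over the whole arm. A 10% sample reported over its own denominator is an equally natural reading. This stands as a limit: the 5–17% arises only if the cases are pooled and the arms are then compared. It does not remove the asymmetry, since on either reading one arm has a source that the other lacks.

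**Usual-care research endoscopies are used elsewhere.** They are, in the missed-BE and benign-conditions rows. That shows the data will exist, which makes leaving them out of this one cell harder to justify.

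**The mortality model.** A reader might infer that the inflated difference feeds endpoint (v), the predicted mortality reduction. The document does not establish this. Endpoint (v) rests on BE prevalence if the test were introduced, and this row lists no data source for it.

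**Missed BE.** A reader might infer that untested intervention patients, 73% at 27% uptake, are wrongly dropped, and that an 82% apparent reduction (0.67% v 3.8%) hides a true one of 23% (3.40% v 2.62% of all patients). The document does not support this. Objective (ii) names tested patients as its comparison group, so no one is dropped from the stated question. The two percentages answer different questions, one about people tested and one about people offered testing. An arm-level replacement would also be weak. At 50% uptake about 342 and 352 patients would be endoscoped, and 3.0% v 3.8% gives z of about 0.6 and power of about 9%. Self-selection into endoscopy would remain.

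**Conclusion.** The asymmetry in the Epidemiology row is in the text, and nothing else in the document repairs it. It departs from the trial's own handling in the primary endpoint (excluded from both arms) and the benign-conditions row (used in both).

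If research cases are pooled with other diagnoses, comparisons on this row are tilted towards the intervention by about 3–10 BE cases on an expected difference of 61, with 4–13 usual-care cases uncounted. This rests on the plan's 4% prevalence, 27% uptake and 85% sensitivity, every TFF3-positive patient being endoscoped, equal arms of 7828, and an assumed endoscopy uptake of 15–50% that is the same in both arms and unrelated to BE status.

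The missed-BE row needs a label, not a replacement. The primary endpoint and the sample size are untouched. The change is worth making because it is specific and cheap, but the matter is secondary.

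**What to change.** 1. **Epidemiology row.** Either list the 10% endoscopy data for both arms or remove them from the intervention cell, as the primary endpoint does. If kept, report them by arm over the number endoscoped and separately from clinical diagnoses. Pooling them into both arms' counts is less satisfactory: usual care would gain 4.0–13.3 cases and the intervention arm 3.1–10.3, which would shrink the difference of 61 by about 1–3 cases.
2. **Missed-BE row.** Keep the stated comparison and say that it is non-randomised. Optionally add a descriptive by-arm estimate of undiagnosed BE from the random 10% samples, including intervention patients who were not tested.

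The cost is wording in Table 2 and a re-tabulation of data already planned for collection. The downside is that the by-arm estimate will be imprecise and should be presented with its interval, not as a test.
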